#### Symptomatic treatment

At the discretion of the medical team, goals for the patient include:To treat and prevent hypersensitivity reactions inherent to venom or antivenom. For this, use:➢ antihistamines – inject intramuscularly, one vial of 50 mg of promethazine or similar option upon the arrival of the patient; repeat every six hours if necessary;➢ corticosteroids – administer intravenously, 200 mg of hydrocortisone or similar option upon the patient’s arrival; repeat every six hours if necessary. This scheme could be maintained for 3 to 5 days, according to the clinical evolution;➢ when anaphylactic shock is suspected – if the patient presents severe hypotension and in the absence of a palpable pulse, inject subcutaneously 500 μg (0.5 mL) of aqueous adrenaline 1:1,000.
Treat the pain: inject intramuscularly, one vial of petidine chlorhydrate 50 mg or similar; repeat every six hours if necessary.In the presence of bronchospasm: utilize a catheter of oxygen (O_2_) associated with bronchodilators of the type β-2-agonist inhalants (salbutamol, phenoterol or terbutaline), at customary doses used at the referring center. Continue as needed until the disappearance of symptoms.

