### Plan of treatment (specific, adjuvant, symptomatic and complementary)

#### Specific treatment

The *WHO Guideline for the production control and regulation of snake antivenom immunoglobulins* [12] suggests that the protocol prepared for the specific treatment be based on the estimated quantity of venom inoculated by the bee and on the neutralizing capacity of the antivenin. Thus, the authors suggested:Up to 5 stings: specific treatment is not indicated, except for a medical criterion.Between 5 and 200 stings: two vials of apilic antivenom.Between 201 and 600 stings: six vials of apilic antivenom.Above 600 stings: ten vials of apilic antivenom.

After the dose is determined by the attending medical team, the vials must be opened and their content aspirated by means of a syringe. Next, insert all the content into a flask containing 250 mL of normal 0.9% saline solution, previously emptied. This flask containing the antivenom must be connected into a Y formation with another flask containing 250 mL of 0.9% saline. One large-caliber vein of the forearm must be catheterized and these two contents need to be infused in the Y within two hours. All patients must be hospitalized and monitored throughout the infusion by the continuous presence of the hospital staff at the patient’s bedside. The team must also have at their disposal the drugs and equipment necessary for the treatment of mild or severe adverse reactions. Any adverse events and signs and symptoms of possible toxicity must be noted on the patient’s chart.

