#### Adjuvant treatment

The adjuvant treatment aims to maintain the patient and avoid hemodynamic shock, preserve kidney function, diminish cerebral edema and prevent the dysfunctions resulting from hemoglobinuria. Thus, the following is proposed:Replenish volume by hydrating patient vigorously with 0.9% saline, after catheterization of a large-caliber peripheral vein, in order to ensure hemodynamic stability. Always maintain arterial pressure levels above 90 × 60 mmHg.Use vasoactive drugs including dopamine and/or noradrenaline to treat hypotension refractory to the volume, at the discretion of the medical staff.Suspect rhabdomyolysis when the level of creatine phosphokinase (CPK) is above 5,000 U/mL. The presence of dark urine, of oliguria and/or anuria may also denote the presence of rhabdomyolysis. In this case the volume of 0.9% saline to be infused will be 20 mL/kg, running freely, being repeatable up to three times. The objective will be to maintain a urinary volume between 2 and 3 mL/kg/hour. Vigorous hydration must be maintained until CPK reaches levels below 1,000 U/mL.In the presence of refractory anuria or oliguria, require an evaluation from a nephrologist for potential hemodialysis.In the presence of electrolytic disturbances such as alterations in levels of Na^+^, K^+^, Ca^++^ or Mg^++^, these parameters should be closely monitored. Hyperkalemia and hypocalcemia, when present, must be corrected according to the protocols of the referring services.

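### The only printed adrenaline instruction for suspected anaphylactic shock requires that no pulse can be felt, so suspected shock with a palpable pulse has no adrenaline instruction

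*Protocol article*

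**What the plan says.** The Symptomatic treatment section of the protocol article opens with "At the discretion of the medical team, goals for the patient include". Its first goal is "To treat and prevent hypersensitivity reactions inherent to venom or antivenom", so it covers infusion reactions as well as reactions to the stings. Three drug items follow under that goal:

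- an antihistamine, "one vial of 50 mg of promethazine or similar option upon the arrival of the patient";
- a corticosteroid, "200 mg of hydrocortisone or similar option", also on arrival;
- subcutaneous adrenaline 1:1,000, 500 μg in 0.5 mL, "when anaphylactic shock is suspected", qualified at once by "if the patient presents severe hypotension and in the absence of a palpable pulse".

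The same section adds oxygen and an inhaled bronchodilator if there is bronchospasm. Adjuvant treatment covers low pressure from any cause. It calls for volume, a pressure kept above 90 × 60 mmHg, and then, at staff discretion, "Use vasoactive drugs including dopamine and/or noradrenaline to treat hypotension refractory to the volume". Specific treatment requires continuous bedside staff during the infusion and adds: "The team must also have at their disposal the drugs and equipment necessary for the treatment of mild or severe adverse reactions".

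The sections that set conduct by number of stings each have a branch for anaphylactic shock. Each branch sends the reader to the symptomatic treatment item and adds no adrenaline rule of its own.

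**The concern.** The adrenaline item names one situation and then prints a condition that fits only its extreme end. A team that follows the text literally would give antihistamine, corticosteroid, fluid and possibly a vasopressor to a participant in suspected anaphylactic shock, and would be prompted to give adrenaline only once no pulse could be felt.

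This matters here for three reasons. Acute hypersensitivity to heterologous serum is the first risk listed under Risks and benefits. The ANVISA approval section says that this is the first time an antivenom against bee stings is evaluated in a human clinical trial. Safety, including the number and severity of acute adverse events, is a primary objective. If earlier adrenaline rests on each team's judgement, the care behind the recorded severity of reactions may also differ between centers. The documents give no means of sizing that effect.

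**Working it through.** No arithmetic result is at issue and the plan states no figure to reproduce. The check is a reading of the text.

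**1. What the condition covers.** Take suspected anaphylactic shock as given and cross the two signs in the printed condition.

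| Severe hypotension | Pulse palpable | Adrenaline prompted as printed | After deleting the pulse clause |
|---|---|---|---|
| yes | no | yes | yes |
| yes | yes | no | yes |
| no | no | no | no |
| no | yes | no | no |

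As printed, the instruction applies in 1 of 4 combinations and in 0 of the 2 with a palpable pulse. Treating the clause as a definition of suspected shock, rather than as a further condition, does not change this. Only reading the conjunction as an alternative would, and the wording does not say that.

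**2. Whether another line fills the gap.** Every mention of adrenaline, anaphylactic shock and treatment of hypersensitivity in the article was read. Adrenaline is named once, in this item. Adjuvant treatment names dopamine and noradrenaline. Specific treatment requires drugs to be available but says nothing on when to use which.

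**3. Whether the protocol itself means shock this narrowly.** The branches for anaphylactic shock suggest not. Under both Up to 200 stings and Up to 600 stings, intensive care for these patients is put only as a possibility. Patients who might not need intensive care cannot all be patients without a palpable pulse. The branches therefore use the term more widely than the adrenaline condition to which they refer.

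**4. How far it reaches.** All four sting-count groups refer to the symptomatic treatment item for shock. In the group with up to five stings antivenom is not indicated, and the abstract enrols people with more than five stings, so that group is set aside. That leaves 4 − 1 = 3 branches that both give antivenom and rely on this line: up to 200 stings (2 vials), up to 600 (6 vials) and more than 600 (10 vials).

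**5. The dose.** A 1:1,000 solution holds 1 mg/mL, and 0.5 mL × 1 mg/mL = 0.5 mg = 500 μg. The dose is consistent with itself and plays no part in the point.

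**The case against.** The strongest reply is that the article does not stop anyone from giving adrenaline earlier. The section is at the team's discretion, and the vasoactive drugs under Adjuvant treatment are introduced as examples, so adrenaline fits there for volume-refractory hypotension. There is a standing duty to hold the pressure, and staff with drugs for severe reactions must be at the bedside. All of this stands. A reader might infer that the protocol withholds or forbids adrenaline while a pulse is present; the text does not support that. What remains is that the one written prompt comes too late. Discretion and stocked drugs do not correct a trigger that is itself misstated.

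Second, the Discontinuation section names a management protocol for acute hypersensitivity without saying that it is this item, and a fuller rule may exist outside the article. That also stands, and it limits the point to the printed condition. A reader might further infer that a participant with a palpable pulse could be judged resistant and discontinued without the protocol ever having called for adrenaline. That would need the two texts to be the same, no discretionary adrenaline to have been given, and a judgement of resistance. The documents establish none of these.

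Third, no passage says that adrenaline is due before the pulse is lost. This is true. That premise is general clinical knowledge and is stated as such. The mismatch between the lead-in, the shock branches and the printed condition is visible without it.

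Fourth, the phrase is loosely built and may be a slip of drafting or translation. That is possible, but a reader at the bedside has only the words, and the conjunctive reading is the natural one.

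Last, this is supportive care with no shown effect on sample size, outcome definition or analysis. That is fair. It is a point of participant safety in a trial whose first objective is safety.

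**Conclusion.** The point holds in a limited form. In the text shown, the only adrenaline instruction for suspected anaphylactic shock requires severe hypotension together with loss of a palpable pulse, and the three shock branches that give antivenom all rely on it. This is a condition stated too narrowly, not a detail lost when the protocol was condensed into an article.

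The size can be given only as reach: 1 adrenaline instruction, 0 that apply while a pulse is palpable, and 3 branches affected. No reaction rate is given and none is assumed, so no number of participants follows.

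The conclusion rests on the literal reading of the conjunction and on the clinical premise that adrenaline belongs before loss of the pulse. It also assumes that no separate hypersensitivity protocol already sets a wider trigger. A reader might go on to infer that suspicion alone should trigger adrenaline at any blood pressure, or that the sequence of volume and then vasopressor under Adjuvant treatment must be reordered. Those are clinical choices open to the investigators. The documents do not show either to be a defect.

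**What to change.** In the adrenaline item under Symptomatic treatment, delete the second half of the condition, the part that requires loss of the pulse. The item would then prompt adrenaline when anaphylactic shock is suspected and severe hypotension is present, whether or not a pulse can be felt. This adds one row of the table above, severe hypotension with a palpable pulse, and changes nothing else.

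The change needs no extra staff, visits or procedures, because Specific treatment already requires bedside staff and the drugs. It has two costs. The Background section lists hypotension among the effects of multiple stings, so some participants whose hypotension comes from the venom may receive adrenaline. The wording must also pass through the amendment process: CONEP approved the protocol, ANVISA received it for analysis and approval, and centers must supply local ethics approval of the current version.

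Dropping the pressure criterion as well, or placing adrenaline ahead of the Adjuvant treatment sequence, can be discussed at the same time but is optional. Deleting the pulse clause alone does neither.

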#### Complementary treatment

Catheterize a large-caliber peripheral vein. In critical patients use central venous access.Apply cardiac monitor and O_2_ saturation meter.Removal of the stingers should be performed immediately after stabilization of the clinical parameters of the patient. The count will help estimate the amount of antivenom to be administered.

#### Other observations

Apply vesical and nasogastric probe when indicated.Apply potassium permanganate diluted 1:40.000, for antisepsis of the skin affected by the stings.Apply enteral feeding containing about 2,000 cal per day when indicated.Maintain fluids, electrolytes and acid–base status as indicated.Perform tracheotomy and/or oral-tracheal intubation with mechanical ventilation, when indicated.Perform peritoneal dialysis and/or hemodialysis, when there is acute kidney failure.Prevent the formation of bedsores.Avoid secondary respiratory infections.

### Conduct according to the number of stings and the presence or absence of anaphylactic reaction

#### Up to five stings

Without anaphylactic shock:➢ remove all of the stingers correctly;➢ prescribe hydrocortisone ointment in isolation or associated with 5% menthol;➢ prescribe dextrochlorpheniramine 6 mg orally, every eight hours as needed;➢ apilic antivenom is not indicated.
In the presence of anaphylactic shock:➢ catheterize access of a large-caliber or central vein to hydrate the patient;➢ follow the protocol contained in the symptomatic treatment item;➢ remove all the stingers correctly;➢ apilic antivenom is not indicated.

#### Up to 200 stings

Without anaphylactic shock:➢ remove all the stingers correctly;➢ catheterize a central vein for hydration of the patient;➢ follow the protocol contained in the symptomatic treatment item;➢ always hospitalize the patient;➢ apply two vials of apilic antivenom.
In the presence of anaphylactic shock:➢ catheterize a central vein for hydration of the patient;➢ follow the protocol contained in the symptomatic treatment item;➢ remove all the stingers correctly;➢ these individuals must always be hospitalized and may require treatment in an intensive care unit (ICU);➢ apply two vials of apilic antivenom.

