**Methods:**

In order to evaluate the safety and neutralizing capacity of a new apilic antivenom, as well as to confirm its lowest effective dose, a clinical protocol was developed to be applied in a multicenter, non-randomized and open phase I/II clinical trial. Twenty participants with more than five stings, aged more than 18 years, of both sexes, who have not previously received the heterologous serum against bee stings, will be included for 24 months. The proposed dose was based on the antivenom neutralizing capacity and the number of stings. Treatment will be administered only in a hospital environment and the participants will be evaluated for a period up to 30 days after discharge for clinical and laboratory follow-up.

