**Fig. 1 Fig1:**
[figure not shown]
Temporal distribution of the number of cases reported for Africanized honeybee sting in Brazil between 2000 and 2015 [4]

The physiopathology of this accident is complex due to the interaction between the diverse toxic components of the venom, the potential target organs and the immune response of the victim [5, 6]. Generally, bee stings can present two different outcomes:Anaphylaxis: occurs in individuals allergic to bee venom. In these cases a single sting can cause serious generalized allergic reactions, possibly leading to death. These consequences are not related to the toxicity of the venom due to the small quantity inoculated. Treatment is limited to general measures and the use of symptomatic drugs aiming to control the anaphylaxis [7].Direct toxicity from the venom: occurs when there are a substantial number of stings – generally more than 200 in adults. In this case, the venom volume is sufficient to cause damage to vital organs. Prominent among the toxic components are melittin and phospholipase A_2_, whose presence accounts for more than 60% of the dry weight of the venom. Direct injury to the cardiovascular, muscular, neurological, dermatological, metabolic, hematological, respiratory and renal systems can lead to death [7, 8].

The clinical manifestations resulting from multiple stings are: generalized pain, intense pruritus, flushing, hyperthermia, papules, urticarial plaques, hypotension, tachycardia, headache, nausea, vomiting, abdominal colic, bronchospasms and psychomotor agitation, which may subsequently evolve to a state of torpor, accompanied by respiratory and cardiac failure and, principally, severe renal failure [8–10]. The most common laboratory alterations are: leukocytosis with neutrophilia, hemolysis, thrombocytopenia, disseminated intravascular coagulation, rhabdomyolysis with increase of creatine phosphokinase (CPK), elevation of the enzymes aspartate aminotransferase (AST) and alanine amino transferase (ALT), increase of urea, creatinine and myoglobin in the urine [8–10].

Mortality is elevated at the extremes of age [4]. In children, due to lower body mass, envenomation can be much more severe, since with many stings the concentration of the toxic components is elevated. In the elderly, greater risk involves such preexisting comorbidities as chronic renal, cardiac or respiratory failure. These constitute an important additional risk factor in patients who are victims of multiple stings.

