## Methods

### Antivenom development and dose proposal

Researchers from the Center for Studies of Venoms and Venomous Animals (CEVAP) of the São Paulo State University (UNESP) in partnership with the Vital Brazil Institute (IVB), Brazil, developed the apilic antivenom. For this, the principal toxins from the venom of Africanized honeybee maintained at the Lageado Experimental Farm, UNESP campus in Botucatu, São Paulo, Brazil, were extracted and purified. Next, previously selected horses were immunized with increasing doses of the chosen antigens. These protocols are described in detail in the developed guide for researchers and in the patent submitted [7, 11].

The proposed dose of the new antivenom was calculated taking into account the premises of the *WHO Guideline for the production control and regulation of snake antivenom immunoglobulins* [12] that prioritize the quantity of venom inoculated in the host, neutralization potency and the proposed antivenom dose. For these calculations, the authors relied on the fact that one bee inoculates during one sting approximately 0.1 mg of venom [1]. According to the serum neutralization tests, each milliliter of standardized antivenom neutralizes 1.25 mg of venom. Therefore, 10 mL of antivenom should neutralize the venom of 100 stings. The experimental validation of antivenom efficacy and preclinical tests are detailed in a paper in progress.

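### A central line is ordered for every participant with up to 200 stings and no shock, against the general access rule, and at 201–600 stings the ICU instruction is weaker with shock than without

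*Protocol article*

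**What the plan says.** **Venous access.** Four places in the protocol article bear on participants with up to 200 stings and no shock.

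- *Up to 200 stings*, branch without shock: "catheterize a central vein for hydration of the patient". No condition or exception is given.
- *Adjuvant treatment*: volume is replaced by "hydrating patient vigorously with 0.9% saline, after catheterization of a large-caliber peripheral vein".
- *Complementary treatment*: "Catheterize a large-caliber peripheral vein. In critical patients use central venous access".
- *Specific treatment*, for the antivenom infusion: "One large-caliber vein of the forearm must be catheterized".

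The same unconditional central-vein order stands in the other five branches of the sections *Up to 200 stings*, *Up to 600 stings* and *More than 600 stings*. By contrast, *Up to five stings* lets a patient who is in shock have either a large-caliber or a central vein.

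**ICU care.** In *Up to 600 stings*, ICU admission is required without exception when there is no shock. When shock is present it is only something the participant might need. *More than 600 stings* uses one wording for both branches: such patients generally require an ICU.

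**The concern.** The two access instructions give different answers for the same participant. Someone with a modest number of stings, no shock and no critical illness is peripheral under the general sections and central under the sting-count section. The article does not say which prevails. Because the antivenom already needs a forearm vein, the central line is a further and more invasive procedure.

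The ICU lines run against clinical order. Within one sting band, the participant in shock is the sicker one, yet has the weaker instruction.

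The stake is participant safety and consistent conduct. All centres in the national research network are to be invited, and standardizing care is one of the study's stated objectives. Centres could follow different sections, each be compliant, and still treat similar participants differently.

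**Working it through.** There is no plan figure to reproduce. The check compares instructions, with a little arithmetic for scale.

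**Step 1. Count the branches.** Three sting bands receive antivenom (up to 200, 201–600, above 600), each split by shock: 3 × 2 = 6 branches.

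**Step 2. Compare access rules.** All six branches order a central vein. The order agrees with *Complementary treatment* wherever the participant is critical. Participants in shock, or with more than 200 stings, may well be critical, so no firm conflict is claimed in those five branches. That leaves one: up to 200 stings without shock, or 1 of 6.

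**Step 3. Ask whether that branch is critical by default.** It excludes shock. The Background places direct toxicity at "generally more than 200 in adults", above the band. The branch itself asks for hospitalization and does not mention an ICU. None of this supports treating everyone in it as critical.

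**Step 4. Scale at the low end.** The abstract's Methods gives the population as "Twenty participants with more than five stings", so the smallest count is 6. *Antivenom development and dose proposal* assumes that "one bee inoculates during one sting approximately 0.1 mg of venom".

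- 6 stings × 0.1 mg = 0.6 mg
- 200 stings × 0.1 mg = 20 mg
- 0.6 / 20 = 3%

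**Step 5. Compare ICU wording within each band.**

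| Band | Without shock | With shock | Weaker with shock? |
|---|---|---|---|
| Up to 200 | Hospital, no ICU line | Hospital, ICU possible | No |
| 201–600 | ICU mandatory | ICU possible | Yes |
| Above 600 | ICU generally required | ICU generally required | No, equal |

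The order is reversed in 1 of 3 bands.

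**Step 6. Participants affected.** The article gives no expected number per branch. For the access point the only bounds are 0 and 20 of the 20 participants.

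**The case against.** The best reply on access is that the sting-count sections come later and are more specific, so a centre may take them as governing. *Complementary treatment* also does not say that central access is for critical patients only. On that reading the order is an aggressive clinical choice, not a contradiction. This softens the conflict but does not remove it: if the specific section governs, a participant with six stings who is not critical still gets a central line, and no reason is given. The comparison with *Up to five stings*, where even shock allows a large-caliber vein, makes that hard to defend.

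It is also fair that the forearm line and the hydration line serve different purposes and can coexist. The forearm line shows only that the central line is an additional procedure.

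Absence of shock does not mean stability. The 200-sting figure is qualified as general, and age and comorbidity add risk, so some participants in this branch may be critical. The order has no exception, however, and so also covers those who are not. The venom arithmetic describes the extreme low end of the band; the article does not tie venom mass to choice of access.

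On the ICU, the weaker wording denies admission to no one, and a floor of care exists. *Specific treatment* states: "All patients must be hospitalized and monitored throughout the infusion by the continuous presence of the hospital staff". *Complementary treatment* adds cardiac and oxygen-saturation monitoring. These points limit the harm, but they do not tell a centre which unit to use or explain the reversal.

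**Conclusion.** Both points hold on the text as it stands. The access conflict is firm in 1 of 6 branches; the other five need only confirmation. The ICU instruction is weaker with shock in 1 of 3 bands, possibly because two lines were transposed.

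The access conclusion assumes that a participant with up to 200 stings and no shock is not critical merely by being in that branch, which the Background supports. The number of participants affected is unknown. This is a matter of participant safety and uniform care that should be corrected. No consequence for the adverse-event outcome, dosing, sample size or analysis is claimed.

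**What to change.** 1. **Up to 200 stings, without shock.** Replace the central-vein line with a large-caliber peripheral vein, and central access only for critical patients. The clinical lead should state what critical means here. One marker already in *Adjuvant treatment* is low blood pressure that does not respond to fluids.
2. **The other five branches.** The clinical lead should confirm whether the unconditional central-vein order is intended.
3. **Up to 600 stings.** Reword so that participants with shock never have a weaker ICU instruction than those without. Swap the two lines if they were transposed, or give both the same instruction; the choice is clinical.
4. **More than 600 stings.** Check this after step 3. If ICU becomes mandatory with shock at 201–600 stings, the present wording above 600 would be weaker for a heavier exposure and should be raised to match. Without shock, that mismatch between the two bands already exists.

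The cost is a small text amendment: one access line, one or two ICU lines, and a check of the remaining access lines and the top band, with further edits if that check calls for them. Because it changes conduct in an approved protocol, it goes through the ethics and regulatory bodies named in the article. Making ICU mandatory in both branches at 201–600 stings would add one mandatory ICU branch; swapping the lines would not add to the count. Raising the wording above 600 stings would make ICU mandatory there too. Sample size, dosing, schedule and analysis are unchanged.
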